## Abstract

**Introduction:** With an increasing number of China's aging population, Parkinson's disease (PD) increases year by year. Persons with PD exhibit abnormal balance functions, leading to motor skills difficulties, such as unstable walking or even falling. Therefore, activities of daily living and quality of life are affected. This study aims to explore the effectiveness of Tai Chi training based on the mobile phone app in improving the balance ability of persons with PD.

**Methods and Analysis:** A randomized, single-blind, parallel controlled trial will be conducted in this study. One hundred forty-four persons with PD who meet the inclusion criteria will be randomly divided into a 1:1:1 ratio: (1) control group, (2) basic experimental group (basic app with no Tai Chi training features), and (3) balanced-enhanced experimental group (basic app with Tai Chi training features). Individuals with PD will be evaluated on balance and motor function outcomes. The primary outcome measure is the limits of stability (including the maximum excursion and direction control); the secondary outcome measures include the Unified Parkinson's Disease Rating Scale III (UPDRS-III), Berg Balance Scale (BBS), Functional Reach Test (FRT), Timed Up & Go (TUG), 6-Minute Walk Test (6MWT), and 39-item Parkinson's Disease Questionnaire (PDQ-39). Each group of patients will go through an assessment at baseline, 17 and 33 weeks.

**Discussion:** This study will evaluate the effectiveness of the mobile phone app Tai Chi training on the balance function of persons with PD. We assume that a challenging Tai Chi project based on a mobile phone app will improve balance in the short and long term. As walking stability progresses, it is expected that daily activities and quality of life improve. These findings will be used to improve the effectiveness of future home management measures for persons with PD.

**Ethics and Dissemination:** This study has been approved by the ethical review committee of the Shanghai University of Sport (approval number: 102772019RT056). Informed consent will be obtained from all participants or their guardians. The authors intend to submit the study findings to peer-reviewed journals or academic conferences to be published.

**Clinical Trial Registration:** Chinese Clinical Trial Registry (ChiCTR2000029135).

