## Materials and Methods

### Study Design and Setting

This study is a single-blind (evaluators), parallel, RCT. Participants will be randomly divided into a control group, a basic experimental group, and a balanced-enhanced experimental group. Assessment will be carried out by the Shanghai University of Sport assessors at baseline, 17 weeks (end of intervention), and 33 weeks (16 weeks after follow-up). The research flowchart is shown in Figure 1. Ethical approval has been given by the ethical review committee of the Shanghai University of Sport (approval number: 102772019RT056, trial registration in Chinese Clinical Trial Registry: ChiCTR2000029135). The study will be performed according to the Consolidated Standards of Reporting Trials (CONSORT) guidelines (35).

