#### Control Group

Participants assigned to the control group will stay on the app's registration screen until the end of the 16-week study period. Therefore, they do not have the right to use any application functions that can help them improve their balance functions, so they will be encouraged to continue their daily activities.

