### Statistical Analysis

Data will be analyzed in an open computing environment, R language, version 3.5.2. Differences between groups of baseline variables will be tested using the chi-square test (categorical variable) and one-way analysis of variance (continuous variable). Repeated measure ANOVA will be used to compare the changes from baseline to 16 weeks among the control group, basic experimental group, and balanced-enhanced experimental group. Pairwise comparisons between the balanced-enhanced experimental group and the two other groups will be conducted only if the omnibus F-test statistics indicated that the null hypothesis should be rejected. An independent sample *t*-test (95% confidence interval) will be used to compare group means. Paired *t*-tests will be used to examine changes within the groups from baseline to 16 and 32 weeks.

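### No between-group analysis is specified for week 33: the only analysis that names the follow-up is a within-group paired t-test

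*Protocol article*

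**What the plan says.** The Discussion paragraph of the Abstract assumes that the app-based Tai Chi programme "will improve balance in the short and long term". Study Design and Setting places assessments at baseline, "17 weeks (end of intervention), and 33 weeks (16 weeks after follow-up"; Table 1 and Outcome Assessment confirm that all primary and secondary outcomes are taken at each of these visits.

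Statistical Analysis assigns methods to times as follows:

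- **Three-group test, dated.** "Repeated measure ANOVA will be used to compare the changes from baseline to 16 weeks among the control group" and the two experimental groups.
- **Pairwise comparisons, gated.** Those of the balanced-enhanced group with the other two groups "will be conducted only if the omnibus F-test statistics indicated that the null hypothesis should be rejected".
- **Independent-sample t-test, undated.** It carries a "95% confidence interval) will be used to compare group means"; no visit is named.
- **Paired t-tests, dated to follow-up.** They "will be used to examine changes within the groups from baseline to 16 and 32 weeks".

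On app access, Control Group keeps those participants on the "registration screen until the end of the 16-week study period". Intervention limits each participant to the features of the assigned group after randomisation, with no end date. Basic Experimental Group bars the Tai Chi module, also with no end date.

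**The concern.** A long-term effect in a randomised trial is a difference between arms at the later visit. Here the between-group window ends at 16 weeks, while the within-group window extends to 32. The two windows stand a few sentences apart in the same paragraph, so this is a stated allocation of methods to times rather than detail left out for space.

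A within-arm change from baseline to follow-up mixes any treatment effect with practice on the balance platform, regression to the mean and disease progression. The control and basic arms are there to remove these influences, and a paired test inside one arm does not use them. Finding significance in one arm and not in another is not a test of the difference between them. If the paragraph is followed as written, a durability statement would have no error control against the comparators.

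**Working it through.** **1. Which analysis reaches week 33?**

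| Analysis | Between groups? | Time stated | Assigned to week 33? |
|---|---|---|---|
| Repeated-measures ANOVA | Yes | Baseline to 16 weeks | No |
| Pairwise comparisons | Yes | Follow the omnibus test; the only one described for outcomes is the 16-week one | No |
| Independent-sample t-test | Yes | None | Not stated |
| Paired t-tests | No | 16 and 32 weeks | Yes, within arm only |

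The 16- and 32-week labels are the ends of the two periods in Table 1 (weeks 1–16 and 17–32). The assessments follow at weeks 17 and 33. This is a labelling mismatch and changes no analysis.

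**2. What can separate paired tests show when there is no treatment effect?**

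Inputs from Sample Size Calculation and the allocation ratio: 144 participants, 15% attrition, 1:1:1. So 144 × 0.85 = 122.4, and 122.4 / 3 = 40.8, about 41 per arm. Alpha is 0.05, taken as two-sided (the article does not say).

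Assumption, not in the article: every arm has the same true change, dz, in units of the SD of change. The range 0.2 to 0.5 is illustrative.

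For one arm, p = P(|T| > t₀.₉₇₅,₄₀), where T is noncentral t with 40 degrees of freedom and noncentrality dz × √41. Arms are independent, so P(Tai Chi significant, control not) = p(1 − p).

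| dz | p | p(1 − p) |
|---|---|---|
| 0 | 0.050 | 0.050 × 0.950 = 0.048 |
| 0.2 | 0.240 | 0.240 × 0.760 = 0.182 |
| 0.3 | 0.466 | 0.466 × 0.534 = 0.249 |
| 0.4 | 0.705 | 0.705 × 0.295 = 0.208 |
| 0.5 | 0.878 | 0.878 × 0.122 = 0.107 |

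With no treatment effect, the Tai Chi arm alone is significant 24% to 88% of the time over this range. The apparently favourable pattern occurs 11% to 25% of the time. A two-sided 5% between-group test would favour Tai Chi wrongly 2.5% of the time.

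**3. What would a week-33 between-group contrast deliver?**

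Take the article's d = 0.25 on the scale of the SD of the quantity compared, with 41 per arm. The standard error of the standardised difference is √(2/41) = 0.221. Power ≈ Φ(0.25/0.221 − 1.96) = Φ(−0.83) ≈ 0.20. The 95% confidence interval would extend about 1.96 × 0.221 = 0.43 SD either side. With 48 per arm (no attrition), power is about 23%.

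**The case against.** **An undated between-group test exists.** The independent-sample t-test follows the sentence on pairwise comparisons and reads most naturally as the tool for them, but nothing confines it to 16 weeks. A reader might infer that week 33 has no between-group test at all; the text does not support that. What stands is narrower: none is assigned to week 33.

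**The week-33 data will exist.** A reader might infer that the long-term question cannot be answered. That is wrong: all outcomes are measured in all randomised arms at week 33, and a contrast can be added without further data collection.

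**The paired tests claim little.** The article says they examine within-group changes and does not say that a group difference will be inferred from them. The percentages above apply only if someone draws that inference, and the assumed equal changes have no source in the article. This is fair, and they are offered only as illustration. The long-term expectation nevertheless has no other analysis dated to support it.

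**Long term is a minor theme.** It rests on one sentence of the Abstract; the hypothesis at the end of Background does not mention it. The end-of-intervention comparison is between groups and is unaffected. This limits the reach of the point but does not remove it.

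**App access.** From the control-group wording a reader might infer that comparators receive the Tai Chi features after week 16 and that the week-33 contrast is diluted. No section says that access opens. Only the control arm has an end point, the other statements have none, and a condensed article may leave this to the full protocol. It is an ambiguity, and the documents give no basis for a dilution figure.

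**Conclusion.** The point holds in its limited form. Statistical Analysis specifies no between-group analysis for week 33, and the only method it dates to follow-up does not use the randomised comparators. The assumed long-term benefit would therefore rest on before-after change. That this is a gap rests on the text alone; the 11% to 25% range rests on 41 per arm, two-sided 5% tests and assumed equal changes of 0.2 to 0.5 SD.

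The finding concerns the written plan, not the data, and it leaves the week-17 comparison untouched. The week labels and the access wording are secondary matters to be clarified in the same revision.

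**What to change.** - Fit baseline, week 17 and week 33 in one model with group-by-visit terms. Report the planned differences (balanced-enhanced against control and against basic) at week 17 and week 33, each with a 95% confidence interval, and state the role of the week-33 comparison.
- Treat the paired t-tests as descriptive.
- Replace the 16- and 32-week labels with the week-17 and week-33 visits.
- Reconcile Intervention, Control Group and Basic Experimental Group on what app access each arm has in weeks 17 to 32, so that the meaning of the week-33 contrast is clear.

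The cost is a change of wording and of model; no new participants or visits are needed. The drawback is precision: at about 20% power for d = 0.25, a non-significant week-33 contrast would not show that the benefit had faded. It should be presented as an estimate with its interval.

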### Data Collection and Management

Assessments will be conducted at the Shanghai University of Sport (Shanghai, China). All assessors will receive proper instructions and guidance regarding all outcome parameters and assessments that will be taken. Research-related information, such as participant identities, data collected, and medical records, will be kept confidential. The CRF will be filled out in the paper form. The data will then be entered and stored in a password-protected electronic database. Another researcher in the team will verify data entry. All data will be monitored and reviewed by the principal investigator or research coordinators. The participants' personal information will only be accessed by the principal investigator of the research to protect patients' confidentiality. The ID list will be safely secured in a locked room for the period of the investigation and thereafter destroyed.

## Discussion

PD not only does reduce the patient's quality of life but also brings a heavy economic burden to society and families (49, 50). Balance dysfunction is the main reason for the increase in individuals' disability rates with PD and the decreased health-related quality of life and survival (51). Many exercise methods are designed to improve the balance ability of persons with PD (52, 53). Studies have shown that Tai Chi combines continuous and complex movements naturally, moves slowly to control multi-directional movement, and controls the COG by moving the bodyweight to focus on the control of dynamic postures (24). Tai Chi training has a beneficial effect on the persons' posture control and has attracted PD persons' attention in the community (54). Tai Chi training can effectively reduce limb stiffness in patients with mild to moderate PD, improve limb flexibility, and significantly increase lower limb strength and stride length. Furthermore, it increases walking speed, reduces the frequency of falls, and effectively improves the patient's gait and balance function (55). Henceforth, scientific physical exercise is of great benefit to persons with PD, which can help improve the balance ability, reduce the risk of falls, and improve the quality of life (52, 56, 57). However, due to the limitation of time and geographical factors, the participation of persons with PD in rehabilitation training is not high.

As smartphones and social media have been embedded in daily life, they provide a promising physical exercise platform in the home environment. Findings from the three-group RCT design, with the inclusion of a control, basic, and balanced-enhanced experimental condition, will allow for detailed examination of the efficacy of app-based PD medication management. In particular, whether the addition of Tai Chi training leads to an increase in balance ability.

Nonetheless, there are some limitations in our trial. This is a single-center study, and the number of participants in our study is not large. The multi-center study design is expected to obtain a larger sample size in the future. Moreover, the lack of patient blinding may increase bias. Participants in the control group may reduce their participation, which will increase the difficulty of recruiting subjects. The number of interventions in the balanced-enhanced experimental group will be recorded automatically by the “Shoupa” app. Conversely, the actual adherence to the intervention needs to be confirmed and followed up by weekly telephone calls. The “Shoupa” app is expected to strengthen the function of video recording to monitor the training compliance of persons with PD.

Information gained from this project has the potential to influence the clinical decisions of doctors and will provide clear evidence as to whether app-based Tai Chi training should be advocated in people with PD. In conclusion, we expect that the presented app-based Tai Chi training in the patients' home-environment will be effective in balance ability.

### Ethics and Dissemination

This study has been approved by the ethical review committee of the Shanghai University of Sport (approval number: 102772019RT056). Written informed consent was obtained from the individual for the publication of any potentially identifiable images or data included in this article (specifically refers to the images in Supplementary Figure 1, not persons with PD). The research team will provide consultation to all participants and their families to answer any study questions. Before signing the informed consent form, the professional Tai Chi teacher will lead the interested patients to conduct two tentative training pieces to better understand this study's intervention process. After the patients and family members fully understand the study process, our team members will organize them to sign an informed consent form or withdraw from the study. Informed consent will be obtained from all participants or their guardians. The authors are inclined to submit the study findings to peer-reviewed journals or academic conferences to be published.

## Ethics Statement

The studies involving human participants were reviewed and approved by the ethical review committee of the Shanghai University of Sport. The patients/participants provided their written informed consent to participate in this study. Written informed consent was obtained from the individual for the publication of any potentially identifiable images or data included in this article.
